## 6. RANDOMIZATION

Patients will be allocated to one of two imaging groups:

| Study Group | Intervention                                                      |
|-------------|-------------------------------------------------------------------|
| 1           | CT Abdomen and Pelvis* + whole body PET-CT†
(Experimental arm) |
| 2           | CT Abdomen and Pelvis* (Standard arm)                             |

\* Usual strategy is contrast-enhanced CT of abdomen and pelvis

† If contrast-enhanced CT of abdomen and pelvis has been done prior to randomization, then a low resolution CT is done with the PET. If a contrast-enhanced CT of abdomen and pelvis was performed within 6 weeks prior to randomization, it is not repeated.

### 6.1. Stratification

Eligible, consenting patients will be stratified by:

- (1) Pre-randomization CT scan abdomen and pelvis *versus* no pre-randomization CT scan abdomen and pelvis
- (2) Pre-treatment pelvic MRI *versus* no pelvic MRI
- (3) Stage of cervical cancer (Stage IB through IIA *versus* Stage IIB through IVA)
- (4) Treatment centre.

### 6.2. Randomization Procedure

Randomization will be conducted centrally by the OCOG Coordinating & Methods Centre (CMC) located at the Henderson Research Centre, Hamilton, Ontario. A minimization technique will be used to allocate patients in a 2:1 ratio (in favour of PET-CT) to receive either pre-treatment whole body PET-CT or no PET-CT scan. This will give the patient a greater chance to receive the experimental intervention with minimal loss of power. After confirmation of patient eligibility and documentation of written informed consent, stratification will be determined by the clinical centre and randomization will be completed by accessing the CMC's web-based Interactive Registration/Randomization System (IRIS). All patients must be registered before any study intervention and/or treatment is started.

## 7. STUDY INTERVENTION

The intervention should be performed within 4-6 weeks from the time of randomization. Women of child bearing potential must undergo a pregnancy test (serum or urine) prior to the study intervention. If the patient is pregnant, they must not undergo the PET-CT.

### 7.1. CT Abdomen and Pelvis + Whole-body PET-CT Group (Experimental arm)

Patients randomized to the experimental arm will undergo pre-treatment whole body F-FDG PET-CT. The imaging strategy will start with a low-dose CT scan to enable definition of the axial field of view and for use in attenuation correction of the emission scan. This will be followed by acquisition of the FDG emission scan. In those patients who have not had a

conventional contrast-enhanced CT scan it would be feasible to subsequently conduct a contrast-enhanced diagnostic CT of the abdomen and pelvis acquired with identical minimal standards to those patients in the CT abdomen and pelvis group. Some of the PET-CT scanners in the trial are capable of performing such CT imaging, but not all can. Hence the contrast-enhanced CT of the abdomen and pelvis can be performed on a separate CT machine (see Section 7.2). The details for the PET-CT + CT imaging protocol have been developed in conjunction with experienced nuclear medicine physicians, physicists and radiologists (see **Appendix VI**). All patients will be required to fast prior to the PET scan and undergo regular monitoring of blood glucose levels by a glucometer prior to receiving the injection of FDG.

## **7.2. CT Abdomen and Pelvis Group (Standard arm)**

Patients randomized to the standard arm will have a conventional CT of the abdomen and pelvis. The minimum standards recommended for CT scans are as follows:

- 5 mm collimation
- helical or spiral scanner technology
- IV contrast in portal venous phase if no contraindications (all injections performed with a power injector at a rate of at least 2cc/s, and contrast dose should be 150ml of [270-300mgI/ml] iodine contrast agent or 2ml/kg up to 200ml). Oral contrast is water soluble, iodinated oral contrast such as MD Gastroview® (Mallinckrodt Inc.) or equivalent, not barium. Typically, a total dose of 600 mL of MD-Gastroview will be ingested.

## **7.3. Post-Imaging Diagnostic Confirmation**

The **primary interpretation of lymph node metastases** should be based on visual criteria:

*Lymph nodes  $\leq 1$  cm in short-axis diameter* (per CT) should be considered positive if there is activity above that of the surrounding background.

*Lymph nodes  $> 1$  cm in short-axis diameter* (per CT) should be considered positive if there is activity greater than blood pool activity. For this purpose, mediastinal blood pool activity can be used as a reference regardless of location of node.

There should also be **recording of SUV measurements** in positive nodes.

SUV should be measured with an ROI to encompass at most 2/3 of the diameter of the node to minimize partial volume effects.

As there may be variability in SUV measurements between different PET centres and between different studies, 2 measurements of SUV of the liver should also be recorded as normal reference. A 3 cm diameter region of interest in the right lobe of the liver should be used for these 2 measurements.

## **7.4. Quality Assurance**

When the OCOG program for the evaluation of PET in oncology commenced in 2002, a quality assurance (QA) program was put in place to establish standards for PET scanners, radioisotopes and interpretation of scans. Initially the PET scans were double read by a primary reader at the clinical centre and an external reader. Any discrepancies were resolved by consensus. In recent years, this process was modified because of the extensive experience gained in over 1600 patients. Currently intermittent checks are performed involving double reads (see *Appendix VII*).

In addition for any new anatomic site (i.e. cervix), for which a new study is commenced, the first 10 patients at each PET participating centre will have their scans interpreted by a primary reader at the centre and a second external reader. Any discrepancies are resolved by consensus. Currently, a provincial physics quality assurance committee meets quarterly to ensure compliance with current guidelines for imaging.

Quality assurance may be performed to assess a sample of the diagnostic CT scans.

## **8. STUDY TREATMENT**

### **8.1. Standard Radiation Therapy for Locally Advanced Cervical Cancer**

The recommended standard radiation is described within this section. Management guidelines based on nodal staging is shown in Table 5. The final treatment plan will be determined by the treating investigator.

#### **8.1.1. Pelvic Radiation**

Whole pelvic external radiation will include 45-50 Gy in 1.8 Gy per fraction for 25 fractions over a period of five weeks. Intracavitary brachytherapy 35-40 Gy will be given in one to two implants low dose rate (LDR) or pulse dose rate (PDR) or 24-30 Gy intracavitary brachytherapy in 3-5 fractions high dose rate (HDR). Parametrial boost 5-10 Gy/1.8-2 Gy/3-5 fractions over 3-5 days to involved parametria will be added if the total dose to the sidewall is less than 60 Gy. Overall treatment time is not to exceed eight weeks.

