##### **8.1.1.1. External Irradiation**

Patients will be simulated and treated in the supine position using immobilization devices as appropriate. CT planning will be performed in all patients to define tumour, clinical and planning target volumes.

Patients will receive 45 to 50 Gy external beam RT delivered to the pelvis in 25 fractions of 1.8 to 2 Gy using 10-25 MV photons. Treatments are to be delivered daily, five fractions per week and should be completed within 5 weeks  $\pm$  3 days. Patients should be treated with their bladder full. If intracavitary RT cannot be performed, shrinking field technique or boost with conventional radiotherapy (CRT)/intensity modulated radiation therapy (IMRT) should be performed to bring gross tumour volume with adequate margins to a minimum of 65 Gy. An attempt should be made to exclude all small bowel from treatment field after 50.4 Gy.

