### Common Iliac and Para-Aortic Fields

Pelvic and para-aortic regions will be treated to a total dose of 40-45 Gy in 5 weeks. Four-field technique (AP-PA and lateral opposed fields) or AP pair will be used. Patients will be treated once a day, 5 days a week with a daily fraction size of 1.8-2 Gy.

Superior border will be a transverse line between T12 and L1 for PA fields, and between L1 and L2 if common iliac nodes are involved. The inferior border will be as per description of pelvic fields above. Lateral border will be 2cm lateral to widest true pelvic diameter unless the distal 1/3 of the vagina is involved; in which case the medial inguinal lymph nodes should also be treated. Custom blocking will be used to shield small bowel and femoral heads while maintaining a margin of at least 1cm from common iliac and PA nodes and should not shield the obturator foramina.

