#### **8.1.1.2 Pelvic Boost**

Following common iliac or para-aortic RT to 40-45 Gy a pelvic boost of a further 5-10 Gy (total 50 Gy) in 1.8-2 Gy fractions may be used for patients with bulky central disease. Fields used will be according to guidelines for pelvic field above.

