##### Determination of Normal Tissue Tolerance

In order to stay below an LDR equivalent of 70 Gy to the rectum (120 Gy) for the 3-5 HDR insertions, including the 45-50 Gy contribution from the external beam radiation, the rectum should receive less than 4.1 Gy for each HDR fraction of 6 Gy (68% of the prescribed dose to Point A). The dose to the bladder should be less than 4.6 Gy per each HDR fraction of 6

Gy (77% of the prescribed dose to Point A). As in LDR brachytherapy, every attempt should be made to deliver tumouricidal doses, even if the late responding tissues receive a slightly higher dose. Brachytherapy volumes and doses will be compared between the two intervention groups.

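### Radiotherapy figures in Section 8 do not agree: pelvic fraction size, para-aortic dose against duration, and the rectal limit at the top of the external-beam range

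*Protocol*

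**What the plan says.** Protocol Section 8.1.1 (Pelvic Radiation) gives the whole-pelvis course as "45-50 Gy in 1.8 Gy per fraction for 25 fractions over a period of five weeks". Section 8.1.1.1 (External Irradiation) gives it as "45 to 50 Gy external beam RT delivered to the pelvis in 25 fractions of 1.8 to 2 Gy" and adds: "Treatments are to be delivered daily, five fractions per week and should be completed within 5 weeks", with a tolerance of 3 days either way.

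Under Common Iliac and Para-Aortic Fields: "Pelvic and para-aortic regions will be treated to a total dose of 40-45 Gy in 5 weeks", treated "once a day, 5 days a week with a daily fraction size of 1.8-2 Gy". No number of fractions is stated there.

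Section 8.1.2 allows an HDR total of 24-30 Gy to Point A in 3-5 insertions of 6-8 Gy. Under Determination of Normal Tissue Tolerance, the aim is to stay below a low-dose-rate (LDR) equivalent of 70 Gy to the rectum, with 120 Gy in brackets, for 3-5 insertions and counting 45-50 Gy of external beam. To that end, "the rectum should receive less than 4.1 Gy for each HDR fraction of 6 Gy". Neither the alpha/beta ratio nor the unit of the bracketed 120 is given.

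**The concern.** Dose, fraction size and number of fractions are tied by multiplication, so a prescription that states all three can be checked directly. Section 8.1.1 fails that check, and the section that follows it gives a different fraction size for the same course. The para-aortic text has a similar tension between dose, daily fraction and duration. The rectal figure is presented as sufficient across the whole external-beam range, which can also be checked.

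Three things are at stake:

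- A centre following the text meets two fraction sizes for one course, and a normal-tissue limit that may not do what its sentence says.
- Section 11.3 excludes complications of radiotherapy from adverse-event recording, so the trial's safety data would not reveal a problem with that limit.
- Section 13.2 postulates extended-field treatment in about 15% of control patients against 25% with PET-CT, so the para-aortic wording would apply more often in the experimental arm. Section 13.1 plans to describe external dose, fractions and duration.

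**Working it through.** **1. Whole pelvis.** Total dose = fraction size × number of fractions.

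- Section 8.1.1: 25 × 1.8 = 45 Gy. The stated 50 Gy is not reproduced; at 1.8 Gy it needs 50 / 1.8 = 27.8 fractions, or 27.8 / 5 = 5.6 weeks.
- Section 8.1.1.1: 25 × 1.8 = 45 Gy and 25 × 2 = 50 Gy. The stated 45-50 Gy is reproduced.

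The total-dose range agrees between the two sections; the fraction size does not.

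**2. Common iliac and para-aortic fields.** Five full weeks at five fractions a week is 25 fractions.

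- 25 × 1.8 = 45 Gy and 25 × 2 = 50 Gy, against a stated 40-45 Gy. The ranges meet only at 45 Gy.
- 40 Gy takes 40 / 2 = 20 to 40 / 1.8 = 22.2 fractions, that is 4.0 to 4.4 weeks. Spread over 25 fractions it would be 40 / 25 = 1.6 Gy each, outside the stated 1.8-2 Gy.

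**3. Rectal limit.** The per-fraction percentages reproduce: 4.1 / 6 = 68% and, for the bladder, 4.6 / 6 = 77%. Five insertions of 6 Gy total 30 Gy and four total 24 Gy, both within Section 8.1.2.

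The protocol gives no conversion, so I assume the linear-quadratic model and read the LDR equivalent as the dose in 2 Gy fractions (EQD2). With r for alpha/beta:

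- BED = n × d × (1 + d / r)
- EQD2 = BED / (1 + 2 / r) = n × d × (r + d) / (r + 2)

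For 25 × 2 Gy plus five insertions at 4.1 Gy, EQD2 = 50 + 20.5 × (r + 4.1) / (r + 2). The last factor exceeds 1 for every finite r and tends to 1 as r grows. The total is therefore never below 50 + 20.5 = 70.5 Gy.

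EQD2 in Gy at the 4.1 Gy limit:

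| alpha/beta | 45 Gy + 5 insertions | 50 Gy + 3 | 50 Gy + 4 | 50 Gy + 5 |
|---|---|---|---|---|
| 2 | 74.0 | 68.8 | 75.0 | 81.3 |
| 3 | 72.3 | 67.5 | 73.3 | 79.1 |
| 5 | 70.4 | 66.0 | 71.3 | 76.7 |
| 10 | 68.3 | 64.5 | 69.3 | 74.1 |
| plain sum | 65.5 | 62.3 | 66.4 | 70.5 |

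Only 50 Gy with five insertions exceeds 70 whatever the alpha/beta. The columns for 50 Gy with four insertions and 45 Gy with five exceed it at 5 and below, not at 10. With three insertions at 50 Gy the total stays below 70 throughout the table (although 3 × 6 = 18 Gy is itself short of the 24 Gy minimum in Section 8.1.2).

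**4. The bracketed 120.** Read as BED at alpha/beta 3:

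- 45 Gy + 5 insertions: 45 × 1.6 + 20.5 × 2.367 = 72.0 + 48.5 = 120.5, about the stated figure.
- 50 Gy + 5 insertions: 83.3 + 48.5, about 132.
- 50 Gy + 4 insertions: 122.1.
- 50 Gy + 3 insertions: 112.4.

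At alpha/beta 4, 50 Gy + 5 insertions gives 75.0 + 41.5 = 116.5, which is below 120.

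**The case against.** Section 8.1.1.1 is the detailed section and it multiplies out, so the slip in Section 8.1.1 can be read as a dropped upper fraction size. A gap of 5 Gy appears only if Section 8.1.1 is read alone. This limits the size of the conflict but does not remove it. The 3-day tolerance would fit 28 fractions of 1.8 Gy (50.4 Gy), but both sections fix the number at 25.

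The para-aortic text states no number of fractions. If five weeks is an outer limit, 40 Gy in 20 to 22 fractions is attainable. That is fair: the fault there is loose wording at the lower end, not an impossible prescription.

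The rectal figure is guidance. The text says less than 4.1 Gy, so the totals above are values at the limit, not for every patient. Under the plain sum the excess is 0.5 Gy, and the same paragraph accepts a somewhat higher dose to late-responding tissue. All this stands. Tolerance for individual departures does not, however, make the limit meet its stated target.

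Three stronger readings are tempting and not supported:

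- A reader might infer that 120 is plainly exceeded. That rests on an assumed alpha/beta of about 3 and an unlabelled number; at 4 or more it is not exceeded.
- A reader might infer that the boost in Section 8.1.1.2 spans 45-55 Gy rather than 50. The stated total of 50 pairs 40 + 10 with 45 + 5, which is consistent.
- A reader might infer that the primary outcome is compromised because Section 12.1 substitutes planned for delivered treatment when the schedule is not completed. That section classifies by intent and field extent, not dose per fraction, and Section 8.1 leaves the final plan to the treating investigator. The patient's own plan is the natural reference.

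**Conclusion.** The point holds, in three parts of unequal strength.

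- **Certain, by arithmetic alone:** Section 8.1.1 yields 45 Gy, not 45-50 Gy, and conflicts with Section 8.1.1.1 on fraction size.
- **Clear, but a matter of wording:** the para-aortic dose and duration agree only at 45 Gy if five full weeks are meant.
- **Conditional on reading the LDR equivalent as EQD2:** at the stated rectal limit, 50 Gy plus five insertions exceeds 70 Gy for every alpha/beta, by 0.5 Gy as a plain sum, 4.1 Gy at alpha/beta 10 and 9.1 Gy at 3. Nothing firm can be said against the 120 until its unit and basis are stated.

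The consequence lies in treatment uniformity, a normal-tissue figure that bears on patient safety, and the reference for a descriptive secondary analysis. The primary outcome, its test and the power are untouched.

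**What to change.** The clinical leads should:

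1. Reconcile Sections 8.1.1 and 8.1.1.1 on fraction size, so that dose, fraction size and number multiply out in both.
2. Reconcile dose, daily fraction and duration under Common Iliac and Para-Aortic Fields, and say whether five weeks is a fixed course length or a limit.
3. Under Determination of Normal Tissue Tolerance, state the alpha/beta ratio and the unit of the bracketed 120, and reconcile the rectal figures with Sections 8.1.1.1 and 8.1.2 over the full range of external-beam dose and number of insertions.

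This review does not say which dose, fraction size or limit is right. Sections 8.1.1.2 and 12.1 need no change on this account. The cost is a protocol clarification, with no effect on sample size or on the primary analysis.

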##### **8.1.1.1. External Irradiation**

Patients will be simulated and treated in the supine position using immobilization devices as appropriate. CT planning will be performed in all patients to define tumour, clinical and planning target volumes.

Patients will receive 45 to 50 Gy external beam RT delivered to the pelvis in 25 fractions of 1.8 to 2 Gy using 10-25 MV photons. Treatments are to be delivered daily, five fractions per week and should be completed within 5 weeks  $\pm$  3 days. Patients should be treated with their bladder full. If intracavitary RT cannot be performed, shrinking field technique or boost with conventional radiotherapy (CRT)/intensity modulated radiation therapy (IMRT) should be performed to bring gross tumour volume with adequate margins to a minimum of 65 Gy. An attempt should be made to exclude all small bowel from treatment field after 50.4 Gy.

### Whole Pelvis Field

The external RT target volume should encompass, with adequate margins, the primary cervical tumour and its gross extension and any grossly involved pelvic lymph nodes as well as possible microscopic extension to pelvic lymph nodes and the uterus. The tumour volume including gross nodal disease should be delineated on the digitally reconstructed radiographs (DRRs) if CT treatment planning is used.

### AP/PA Pelvic Fields

The superior border will be through the L5-S1 interspace unless the target volume would not be encompassed adequately in a cephalad direction. In this case, a 2cm margin should be added to the highest level of pathologic abnormality, but should not be cephalad to the L-4/L-5 interspace. The lateral border will be 2cm beyond the lateral margins of the bony pelvis. The inferior border will be inferior to the obturator foramen or the lowest extension of disease with at least a 3cm margin. The inferior extent of cervical cancer or vaginal extension should be marked so that the inferior border of disease can be documented. Uninvolved normal tissues may be blocked although the position of the uterus should be contoured to ensure adequate coverage. Multi-leaf collimator (MLC) or custom Cerrobend blocks are acceptable for field shaping.

### Lateral Pelvic Fields

The anterior border should be at the anterior symphysis pubis, and the posterior border will be through the posterior sacrum to include the cervical disease with a margin of 3-4cm. Superior and inferior borders will be the same as for the anterior and posterior fields. At least 3cm should not be blocked anterior to the L-5 vertebral body. Also the anterior two-thirds of the L-5 vertebral body should not be blocked. Posterior blocking should be designed such that gross disease is encompassed with at least a 2.5cm margin. The outer table of the sacrum should be blocked to protect the sacral plexus on lateral fields.

### Common Iliac and Para-Aortic Fields

Pelvic and para-aortic regions will be treated to a total dose of 40-45 Gy in 5 weeks. Four-field technique (AP-PA and lateral opposed fields) or AP pair will be used. Patients will be treated once a day, 5 days a week with a daily fraction size of 1.8-2 Gy.

Superior border will be a transverse line between T12 and L1 for PA fields, and between L1 and L2 if common iliac nodes are involved. The inferior border will be as per description of pelvic fields above. Lateral border will be 2cm lateral to widest true pelvic diameter unless the distal 1/3 of the vagina is involved; in which case the medial inguinal lymph nodes should also be treated. Custom blocking will be used to shield small bowel and femoral heads while maintaining a margin of at least 1cm from common iliac and PA nodes and should not shield the obturator foramina.

### Lateral Common Iliac and Para-Aortic Fields

Anterior border will be anterior to the symphysis pubis and at least 1cm anterior to common iliac or PA nodes. Posterior border: will be through the posterior sacrum to include the cervical disease with a margin of 3-4cm; blocking should split the T12-L5 vertebral bodies

to shield posterior soft tissue and may split the sacrum to provide adequate margin for presacral nodes; posterior blocking should be designed so that gross disease is encompassed by at least a 3cm margin. Custom blocking will be used to shield small bowel.

#### Dose Specification

The dose to the pelvis shall be calculated at the intersection of the axes of the 4 field box or at midplane of an AP pair. The dose to point B shall also be calculated using an off axis calculation (or identified on isodose distribution). The dose to central structures shall be the sum of the dose at the intersection of the axes of the 4 field box and the dose to point A from the intracavitary treatment. The dose to sidewall structures shall be calculated bilaterally and shall be the sum of the dose at the intersection of the axes from the 4-field box plus the intracavitary dose to each point B plus the contribution from the parametrial fields.

#### **8.1.1.2 Pelvic Boost**

Following common iliac or para-aortic RT to 40-45 Gy a pelvic boost of a further 5-10 Gy (total 50 Gy) in 1.8-2 Gy fractions may be used for patients with bulky central disease. Fields used will be according to guidelines for pelvic field above.

#### **8.1.2. Intracavitary Brachytherapy**

##### Low Dose Rate or Pulse-Dose Rate (LDR/PDR) Brachytherapy

Following the completion of whole pelvic RT the patient will receive 35 to 40 Gy to Point A by intracavitary implant. The patient may receive this in one or two applications at the discretion of the radiation oncologist. The first insertion should be performed promptly upon completion of whole pelvic RT. If two implants are contemplated, the second implant should be completed within three weeks of the completion of whole pelvic RT.

